# Protocol of identical exercise programs with and without specific breathing techniques for the treatment of chronic non-specific low back pain: randomized feasibility trial with two-month follow-up

**DOI:** 10.1186/s12891-023-06434-6

**Published:** 2023-05-05

**Keywords:** Breathing exercise, Breathing techique, Movement control exercise, Chronic low back pain, Yoga, Pilates

## Abstract

**Background:**

Chronic low back pain (CLBP) is a leading cause of disability globally. Exercise therapies are one of the commonly prescribed treatment options for CLBP. The specific exercise therapies for CLBP most commonly target movement dysfunction, but seldom brain-based pain modulation. Exercise therapies with specific breathing techniques (SBTs) have been shown to influence and enhance brain-based structural and functional pain modulation.

**Aims and objectives:**

To assess the feasibility of the SBTs protocol, eligibility criteria, randomization, and dropout rates. To quantify the changes in patient outcome measures and choose the most relevant measure for larger-scale study. To quantify self-adherence levels to home exercise and monitor and record possible pain medication and other treatment modality usage, and adverse events during exercise.

**Design:**

A parallel randomised analyst-blinded feasibility trial with two-month follow-up.

**Outcome measures:**

Feasibility related to aims and objectives. Multiple pain- and health-related patient-reported outcome measures of pain intensity, disability, central sensitization, anxiety, kinesiophobia, catastrophising, self-efficacy, sleep quality, quality of life, and health and well-being status. Exercise adherence, pain medication and other treatment modality usage, and possible adverse events related to exercises will be monitored and recorded.

**Methods:**

Thirty participants will be randomized to movement control exercise with SBTs (15 subjects in experimental group) or movement control exercise without SBTs (15 subjects in control group) in private chiropractic practice setting with two-month follow-up. Trial registration number; NCT05268822.

**Discussion:**

The clinical difference in effectiveness between practically identical exercise programs in uniform study settings with or without SBTs has not been studied before. This study aims to inform feasibility and help determine whether progression to a full-scale trial is worthwhile.

**Supplementary Information:**

The online version contains supplementary material available at 10.1186/s12891-023-06434-6.

## Introduction

Chronic low back pain (CLBP) is a leading cause of disability globally, with enormous personal, social and economic burdens [1]. The transition to CLBP is usually preceded by several episodes of low back pain of varying lengths and intensity [2]. Biopsychosocial factors, including genetic predisposition, lifestyle factors, pain modulation factors, and several chronic disease comorbidities, are known contributory factors to the development of CLBP over time [1, 3]. Exercise therapies are one of the most commonly prescribed treatment options for CLBP, although the effect sizes are small to moderate [4]. Generally, management of CLBP is very challenging and require new, simple, more effective, less costly, and safe exercise approaches to promote more effective management strategies [5].

The most specific exercise therapies for CLBP concentrate on biophysical output mechanisms such as treatment of motor control because chronic musculoskeletal pain is associated with impaired motor control [6–9]. Among the most studied and most evidence-based and CLBP guideline–recommended approaches to assess and treat motor control are the low back movement control tests and exercises of Luomajoki et al. [10, 11]. The reliability of assessment and well-documented exercises for the treatment of movement control impairment make this exercise approach easily applicable for study with practically identically tested and treated exercise groups [10, 12–14]. The main clinical challenge from an effective pain treatment perspective is that the exercises target impaired motor function, but not well-documented abnormalities on central nociceptive structures and functional changes [15–20].

Yoga and Pilates emphasise the importance of different specific breathing techniques (SBTs) with exercise in the treatment of chronic musculoskeletal pain [21–23]. These body–mind interventions are increasingly popular, researched and implemented in healthcare settings to treat pain [23–25]. Exercises with SBTs have been shown to potentially enhance multiple brain-based structural and/or functional changes confirmed on imaging studies [26–29]. These brain-based positive changes overlap negative changes related to chronic pain seen in imaging [30–32]. In clinical studies, the effectiveness of exercises with SBTs are multifactorial, addressing multiple biopsychosocial factors contributing to the development and persistence of CLBP [33–40]. Moreover, exercises with SBTs appear safe or safer when compared to other exercise types [41, 42]. However, the mechanisms underlying the multifactorial clinical effectiveness of exercises incorporating SBTs are sparsely studied and barely understood [24, 25, 43–45]. Furthermore, studies of yoga are generally conducted with very heterogeneous SBTs protocols and include many other types of practices [46]. Because of the heterogeneity of study protocols, it is hard to determine the effect of SBTs alone on clinical outcome differences compared to exercise without SBTs for different chronic pain syndromes.

There are no previous studies that have compared the outcome of identical exercises with or without SBTs in a uniform clinical study setting to inform differences in multifactorial patient-reported outcome measures (PROMs). Hence, this study aims to inform feasibility and help determine whether progression to a full-scale trial is worthwhile. With positive outcomes from this feasibility study and following a full-scale randomized controlled trial with several therapy providers and guideline-recommended pain patient education, SBTs could become a valuable add-on to almost any specific exercise therapy treating chronic pain. SBTs can be implemented for exercise therapy in everyday clinical practice with minimal extra training for therapists, without extra costs, without any extra equipment and without extra side effects or risks of injury for participants.

### Objectives

To assess the feasibility of a clinical study protocol, including an SBTs protocol, eligibility criteria, randomization and dropout rates.To quantify the changes in PROMs to help determine whether progression to a full-scale trial is worthwhile and to inform the choice of the most relevant and responsive PROM for a larger-scale study.To quantify self-adherence levels to home exercise and to monitor possible pain medication and other treatment modality usage, as well as possible adverse events and injuries during exercise using a home diary.

## Methods

### Trial design

A parallel randomised analyst-blinded feasibility trial with two-month follow-up. The study will be carried out in a single private chiropractic clinic. The study is a single blinded as administer will not be blinded for study intervention.

Thirty participants after meeting eligibility criteria will be allocated to movement control exercises with SBTs (experimental group) or movement control exercises without SBTs (control group) with an allocation ratio of 1:1.

**Fig. 1 Fig1:**
[figure not shown]
CONSORT 2010 flow diagram

### Participants

#### Eligibility criteria

The participants will be eligible for the study if they meet all inclusion and no exclusion criteria.

Inclusion Criteria:Males and females aged 18–68 yearsLow back pain lasting more than 3 months (pain sensation more than 3 days per week)A numerical pain scale of 4 or higher on a scale of 0 to 10 to prevent floor effects in outcome measurement [47]Roland-Morris Disability Questionnaire score of 5 or higher on a scale of 0 to 24 to prevent floor effects in outcome measurement [48]Physically able to perform movement control tests and provide written informed consent ≥ 2/6 positive low back movement control tests as described by Luomajoki et al., which are well-documented and valid tests of movement control dysfunction on participants with CLBP [12, 13, 49]. The tests are:Waiters bow test for assessment of flexion movement control impairmentDorsal tilt of pelvis for assessment of extension movement control impairmentOne leg stance for assessment of lateral flexion and/or rotational movement control impairmentSitting knee extension for assessment of flexion or rotational movement control impairmentRocking backwards for assessment of flexion movement control impairment and rocking forwards for assessment of extension movement control impairmentProne lying active knee flexion assessment of extension and/or rotational movement control impairment

Exclusion Criteria:Any history of malignancyNeurological disease affecting the central nervous system (MS, dementia)Rheumatic disease (fibromyalgia, ankylosing spondylitis/rheumatoid arthritis)Chronic obstructive pulmonary disease or other diseases that affect the lungs and cause breathing problemsSpinal surgery in the last 12 monthsA cardiac pacemakerPregnancy during the data collectionSigns and symptoms of lumbar nerve root pathology during the eligibility assessment following neurological examination.aToe and heel walk three metresbLower extremity reflexescSitting Slump testsdFemoral nerve stretches tests on side lyingeSupine active and passive straight leg raises on ipsi- and contralateral legs

The main aim of the inclusion and exclusion criteria is to attempt to minimize the effect of intervention differences by including only participants with movement control impairment. Exclusion is based on standardized and reliable low back movement control tests by Luomajoki et al. [12, 13, 49]. Furthermore, treating specific movement control impairment with standardized exercises is an attempt to minimize difference in effect size, exercise variation and physical performance heterogeneity between the groups. A second aim of the tight eligibility criteria is to exclude known cardiovascular, respiratory, rheumatic and neurological diseases potentially affecting breathing mechanics. The eligibility criteria for the neurological examination aim to minimise group difference heterogeneity to include only participants with non-specific CLBP and exclude participants with nerve root pathology due to intervertebral disc herniation or lumbar spinal stenosis, using an established, recommended, reliable and comprehensive neurological examination [50]. Signs and symptoms of possible nerve root pathology are based on the first author’s clinical decision and participants with a high probability of nerve root involvement will be excluded.

#### Recruitment

The research advertisement for the clinical trial will be presented on the first author’s private clinic webpage. In addition, different national Finnish musculoskeletal pain and spine-related organisations, chronic pain peer support groups, and healthcare colleagues will promote the study on their web pages and social media.

Potentially eligible patients meeting the criteria for this study will be invited to read the participant information sheet and consider enrolling in the study. Enrolled participants will book eligibility assessment appointments at the first author’s clinic, where written consent for the study will be given. After written consent, neurological examination of nerve root pathology and low back movement control clinical tests as described by Luomajoki et al. [12, 13] will be carried out as described in detail above.

After the eligibility assessment, the study participants will complete study questionnaires on the webpages of Navisec Health at home. Navisec Health is a Finnish company providing an electronic platform with strong electronic authentication for data collection and storage of study questionnaires for participants. In Finland, strong electronic identification enables participants to verify their identity safely in various electronic services before filling in PROMs.

The participants meeting inclusion and exclusion criteria will be invited by email to book the first research appointment from the internet time booking calendar. We anticipate needing 120 participants with CLBP to complete the clinical eligibility assessment and the study PROMs to recruit 30 participants. The sample size of 30 participants is a general recommendation for feasibility and pilot trials [51]. The sample size calculation for this feasibility study will not be calculated, because it is not recommended when there is no previous data from previous studies of similar study setting to inform this process [52].

#### Randomization procedure

Thirty participants will be allocated by simple randomization prior to start of participant recruitment, with an allocation rate of 1:1. The random allocation list will be generated by the first author using the SPSS program. The participants will be included in the study in order of meeting the inclusion criteria and no exclusion criteria. They will subsequently book their first research appointment via the internet calendar booking system according to their timetables. Hence, the first author will be unable to decide in advance on the allocation group of the participant. Participants are blinded for intervention differences between groups.

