#### Shared in-clinic treatment protocol for both groups

A single clinician (the first author) will administer the assessment and treatment of movement control exercises to both groups. The first author is an experienced and long-term clinician in treating chronic musculoskeletal pain with exercises and breathing exercises. The advantage of this single-clinician study design is its ability to minimise the intervention differences and effects of contextual factors, such as clinic environment, location, architecture, interior design and therapists’ behaviour, communication and attitudes, which are well established as having a major effect on therapeutic placebo and/or nocebo effects in clinical encounters [76, 77].

After allocation to groups, each subject will be asked to attend four one-to-one contact sessions (30 min per session) on an individual basis over eight weeks. The most commonly anticipated in-clinic research appointment frequency is one week after the first session (week 2/8 in the study), two weeks later (week 4/8 in the study) and two weeks after that (week 6/8 in the study).

For both groups in the research appointments, visual demonstration, verbal guidance and/or hands-on assistance will emphasise the importance of motor learning focused on precision of movement control according to individual subject impairments. The primary goal of movement control intervention is to retrain optimal movement control and coordination of the spine, pelvis, hips and limbs to avoid ongoing nociceptive input secondary to suboptimal tissue loading [8].

The movement control exercises are intended to treat flexion (nine different exercise candidates), extension (nine different exercise candidates) and/or lateral flexion–rotational movement impairments (five different exercise candidates), as shown in Table 2. Two out of 23 exercises (camel and cat exercises) are more stretching type of exercises, in which the movement control exercise aim is to learn to return to a neutral spine after stretching. The exercises are mainly adapted from previous studies and the movements control handbook for treating CLBP by Luomajoki [14, 78, 79].

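### The first author makes the allocation list, judges eligibility and treats both groups, so upcoming assignments can be foreseen, and online self-booking does not prevent this

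*Protocol article*

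**What the plan says.** All references are to the protocol article.

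- **Randomization procedure, timing and method:** "Thirty participants will be allocated by simple randomization prior to start of participant recruitment, with an allocation rate of 1:1".
- **Randomization procedure, who makes the list:** "The random allocation list will be generated by the first author using the SPSS program".
- **Randomization procedure, how participants enter:** "The participants will be included in the study in order of meeting the inclusion criteria and no exclusion criteria". Then: "They will subsequently book their first research appointment via the internet calendar booking system according to their timetables".
- **Randomization procedure, conclusion drawn:** "Hence, the first author will be unable to decide in advance on the allocation group of the participant".
- **Eligibility criteria:** "Signs and symptoms of possible nerve root pathology are based on the first author", that is, on this person's "clinical decision and participants with a high probability of nerve root involvement will be excluded".
- **Recruitment:** consent, the neurological examination and the movement control tests take place at the first author's clinic. Participants then complete the study questionnaires at home on an external electronic platform. Those who meet the criteria are invited by email to book. About 120 people are expected to be assessed to obtain 30.
- **Section on the shared in-clinic treatment protocol, who assesses and treats:** "A single clinician (the first author) will administer the assessment and treatment of movement control exercises to both groups".
- **Table 1:** progression to a full trial looks, among other things, at clinically relevant PROM differences between groups and at balance in numbers and demographics after randomisation.

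**The concern.** Random allocation protects a comparison only if whoever decides on entry cannot see which arm comes next. Here one person produces the sequence, makes a discretionary entry judgement and delivers both treatments. Someone who knows that the next slot is experimental may, without intending it, read a borderline nerve root sign differently than if the next slot were control.

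The article does not leave this open. It offers a specific reassurance and derives it from self-booking, which does not support it. A reader planning the full trial could carry the procedure forward as sound.

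At stake are the between-group PROM differences and the group balance that Table 1 uses for progression. Blinding the data analyst does not help, because it acts after participants have been selected. The Strengths and limitations section names the single-clinician design and the lack of intervention blinding, but not foreseeable allocation.

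**Working it through.** The article states no figure on this point that could be reproduced. The check is to follow the stated steps in order and ask what the list generator knows at each.

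1. **Before recruitment.** The whole list is fixed and the first author generates it. The article describes no step that takes it out of that person's sight.
2. **Clinic assessment.** The first author decides on nerve root exclusion. The upcoming entries already exist and are available to that person.
3. **Home questionnaires.** The pain threshold (4 or higher) and disability threshold (5 or higher) are inclusion criteria. If they are read from the home questionnaires, as the order of steps suggests, eligibility is not settled at the examination. When several people are pending, it is uncertain which of them takes the next slot. The content of that slot is not hidden.
4. **Inclusion.** Slots are filled in the order in which people meet the criteria.
5. **Self-booking.** This comes after inclusion and sets the time of the appointment.

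**Does the conclusion follow from step 5?** There are two ways to read how a slot is taken.
- *Order of meeting the criteria (as stated).* Booking plays no part in assigning the slot, so it cannot be the safeguard.
- *Order of booking.* The participant's timing then affects which slot is taken, so prediction is less exact. The generator still has the list and can see whose booking meets which entry.

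The safeguard fails on both readings. A list fixed in advance does prevent directly choosing an arm for a given person. It does not prevent foreknowledge of the arm while deciding whether that person enters.

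**Room for selection.** Inputs from Recruitment: 120 assessed, 30 included.
- Yield: 30/120 = 25%.
- Assessed per slot: 120/30 = 4.
- Not included: 120 − 30 = 90, with no split by reason.

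**Illustration (assumed, not from the document).** Suppose prognosis is normally distributed and a share q of inclusions in each arm is steered, towards the better half in one arm and the worse half in the other. The mean of a half-normal is √(2/π) = 0.798 SD, so the expected imbalance is 2 × q × 0.798 SD.

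| q | Imbalance (SD) |
|---|---|
| 5% | 2 × 0.05 × 0.798 = 0.08 |
| 10% | 2 × 0.10 × 0.798 = 0.16 |
| 20% | 2 × 0.20 × 0.798 = 0.32 |
| 30% | 2 × 0.30 × 0.798 = 0.48 |

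With 15 per arm, the standard error of a difference in means is √(2/15) = 0.37 SD. Even the largest value is about 0.48/0.37 = 1.3 standard errors, so it would be hard to tell from chance. It would enter the outcome difference only as far as the steered characteristic predicts the outcome.

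**The case against.** Several points against the concern have force.

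- **The article never says that allocation is concealed.** A reader might infer a false claim of concealment. The wording is that the first author cannot decide the group in advance, and in the narrow sense of choosing an arm for a person that is defensible. What stands is that the inference is inadequate, because foreknowledge remains.
- **The next assignment is not certain at every judgement.** It is tempting to say that all 30 assignments are known as each person is examined. The home questionnaires come after the examination, so the order in which people qualify depends partly on them. This weakens prediction but does not remove it.
- **Little of the exclusion may be discretionary.** Many criteria are self-reported scores or diagnoses, and the article describes the movement tests as standardised and reliable. Only the nerve root exclusion is stated to be a clinical decision. The 90 people not included therefore cannot be read as 90 opportunities for judgement.
- **Imbalance is not wholly invisible.** Baseline PROMs and demographics are collected and balance is examined, so it would be too strong to say that the bias cannot be detected or corrected. Measured imbalance can be described and partly adjusted for; unmeasured prognosis cannot.
- **This is a small descriptive feasibility trial.** The randomisation question it asks is about balance, and between-group differences are one of six Table 1 rows. That limits the consequences, but both items are progression criteria.
- **A fuller protocol might describe custody of the list.** That is possible. The point rests on what the article states and the conclusion it draws, not on silence about custody.

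**Conclusion.** The concern holds in a limited form. As described, the person who generates the list can foresee upcoming assignments while judging eligibility. Self-booking after inclusion does not prevent this, so the sentence beginning with the word Hence should not stand. The home questionnaires reduce certainty about who takes the next slot without hiding the list.

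The possible selection bias bears on the between-group PROM differences and on group balance. Its size cannot be derived from the document: the 0.08 to 0.48 SD range depends entirely on the assumed share of steered inclusions. No bias in points on any scale, and no fraction of a minimal clinically important difference, can be supported. Nothing in the article suggests intentional manipulation, and the point does not need it.

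The correction is worth making before recruitment because it is cheap and protects two progression criteria.

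**What to change.** **If allocation has not started:**
- Have an existing team member with no role in eligibility or treatment generate a new list and hold it under neutral arm codes. A list the first author has already seen cannot be made concealed by rewording.
- Release each assignment only after eligibility is recorded as final and the baseline PROMs are complete.
- Replace the sentence beginning with the word Hence with a description of this release step.

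The article describes the platform operator's service as data collection and storage, so it should not be assumed that the operator can randomise.

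The cost is a wording change, a new list, and one message or sealed envelope per participant, with no additional visits or patients.

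One limit remains. The Abstract gives 15 per group, whereas the Randomization procedure specifies simple randomisation. The therapist sees past assignments. If the list is forced to 15/15, the best guessing strategy would be right about 15 + 2^29/C(30,15) − 0.5 = 17.96 times in 30 even with a third-party holder, against 15 in 30 for an unrestricted list. The new list's type should be stated.

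**If allocation has already started:** withdraw the sentence, and report the lack of allocation concealment as a limitation when the between-group differences are read.
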